### Data monitoring

Regular team meetings will be held to monitor the progress of the study and set timelines and will allow for any issues to be discussed and resolved. All data will remain secure and de-identified, which the primary investigator will ensure in addition to data cleansing and circulation of results/outcomes.

### Data storage

Collected electronic data will remain secure through password protection on University of Queensland servers. Filing cabinets containing patient data will remain locked and secured within the swipe card-accessed Centre for Children’s Health Research. All data collected for the purpose of this investigation will be accessible only by the primary investigator and approved names on the ethics application form. Data collected and used for the trial will be de-identified, cleaned and checked. Any missing data will be coded as missing, unknown or not applicable before being locked for analysis. Data will remain secure for 15 years as per the requirements of The University of Queensland HREC.

### Sample size

The sample size estimate was calculated on the basis of the primary outcome of pain intensity after dressing application. Previous researchers assessing paediatric burn pain reported that pain scores within each subject group were normally distributed with an SD of 2.4 [37]. To detect a significant between-group difference of 1.8 in pain scores after dressing application, 29 experimental participants and 29 control participants will need to be recruited in order to reject the null hypothesis that the population means of the experimental and control groups are equal with probability (power) of 0.8. The type I error probability associated with the test of this null hypothesis is 0.05. With up to a potential 20% loss to follow-up, the calculated target sample size is equal to 72 participants. LCCH treats approximately 25–34 children per month in the DEM for acute burn injury. On the basis of these estimates and a historical 70% success rate for trial recruitment within LCCH, it is predicted that around 17 patients will be recruited per month. Therefore, it is estimated that data collection should be completed within 12 months from recruitment commencement.

### Data analysis

The data set will be analysed using IBM SPSS Statistics software (version 22; IBM, Armonk, NY, USA) and Stata software (StataCorp, College Station, TX, USA). Descriptive statistics will be calculated for all outcomes. Univariate parametric analyses (e.g., *t* test, chi-square test) or alternative non-parametric equivalent tests (e.g., Mann-Whitney *U* test) will be used to assess differences between groups at baseline where appropriate. Between-group differences in outcomes will be analysed using regression models. When analyses include multiple measures on the same participant, mixed effects methods will be used to account for probable non-independence in observations. When outcomes are on an interval scale, linear models will be used. When outcomes are binary, logistic models will be used, and when outcomes are recorded as count data, Poisson models will be used. Sensitivity analyses will be undertaken using multiple imputation methods, where it can be assumed data are missing at random. Analysis of differences between groups, and also differences within groups over time, will be undertaken. Analyses will be done on an intention-to-treat basis. Significance will be set at *p* < 0.05.

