### Hypotheses

It is hypothesised that Burnaid® is more effective than plastic wrap at reducing pain intensity in the acute burn phase. It is also hypothesised that decreased pain experienced during the acute phase of the burn injury will speed up wound healing time and will result in a clinically significant reduction in days to full re-epithelialisation after application in children after a burn.

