### Exclusion criteria

Exclusion criteria for mechanism of injury are chemical, electrical, inhalation or friction burns; children who do not arrive within 24 h of sustaining their acute burn injury; children who do not receive appropriate first aid treatment; children who received prior treatment of a silver dressing or ointment; children who are non-English-speaking; children with cognitive impairments; children who are ventilated or require initial wound care in theatre for debridement or grafting; current involvement with the Department of Communities (child safety); children with known sensitivity to hydrogels or hypersensitivity; and children who have co-morbidities that would potentially impair would healing (e.g., diabetes) or that may exacerbate itch and pain.

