### Secondary outcome measures

#### Days to re-epithelialisation

The number of days from the date of the initial burn until 95% wound re-epithelialisation occurs, the surface area of the affected area, and the percentage of wound re-epithelialisation will be calculated using three methods: (1) clinical judgment of the treating consultant, (2) 3D photography (3D LifeViz™ System; QuantifiCare, Valbonne, France) and analysis using specialist computer software, and (3) blinded review of the 3D photographs by a panel of burn specialists. The 3D LifeViz™ System will be used to photograph all burns upon first presentation to the hospital following wound debridement and at each subsequent burns OPD visit for dressing changes and wound care. This will be performed for all participants until burn wounds are deemed to be 95% re-epithelialised or are grafted. Research has found 3D photography to be a valid and reliable measure of acute burn wound surface area in an Australian paediatric population [54, 55]. In order to ensure accurate measurement calibration in the associated DermaPix™ software package (QuantifiCare), a ruler will also be included in all 3D photographs. The 3D images will be analysed by the primary investigator using the DermaPix software programme to determine the surface area of the burn and the area of re-epithelialisation of the wound at each COD. A panel of burn specialists, which will be composed of consultants and nursing staff, will perform a blinded review of the 3D images and will assess the level of re-epithelialisation and appearance of each participant’s burn, mapping out the edges of the wound and all unhealed areas. We will further examine concordance between the burn specialist’s clinical assessment and the DermaPix mapping programme regarding re-epithelialisation.

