#### Adverse effects

The proposed intervention is considered to be part of standard pre-hospital care and is currently used by Queensland Ambulance Services, despite Burnaid® products not being used at the LCCH DEM and burns OPD. Therefore, minimal adverse events are expected. Known potential adverse events (such as hypothermia, infection, haematoma, excessive exudates, unpleasant sensations, allergic reactions, chondritis, and disruption of the skin on dressing removal) have a standardised management protocol at LCCH DEM and burns OPD. In addition, children with known adverse reactions to hydrogels will be excluded from the trial. Adverse effects of the hydrogel dressing will be monitored by reviewing patient medical records and via self-report data from parents/caregivers, participants (where appropriate), and treating clinicians. All adverse events will be reported to the clinical health service and the overseeing HREC. If a consultant believes that Burnaid® hydrogel dressings were not appropriate for a patient’s treatment, discontinuation or alteration of treatment will be at their discretion, and data collection for such participants will cease from that time point.

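### Days to re-epithelialisation is a time-to-event outcome that grafting or loss can cut short, but the stated models all need an observed healing day

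*Protocol article*

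**What the plan says.** The secondary outcome in the section Days to re-epithelialisation is "The number of days from the date of the initial burn until 95% wound re-epithelialisation occurs". On the 3D photography that tracks the wound, the same section says: "This will be performed for all participants until burn wounds are deemed to be 95% re-epithelialised or are grafted". The Hypotheses section makes this outcome the second hypothesis: less pain in the acute phase "will result in a clinically significant reduction in days to full re-epithelialisation".

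Two other passages affect who reaches an observed healing day:

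- Exclusion criteria removes "children who are ventilated or require initial wound care in theatre for debridement or grafting". This concerns initial care only, so grafting later in follow-up remains possible.
- Adverse effects says that if a consultant judges the hydrogel unsuitable and stops or alters treatment, "data collection for such participants will cease from that time point".

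Data analysis assigns models by type of outcome. "When outcomes are on an interval scale, linear models will be used"; logistic models serve binary outcomes; and "when outcomes are recorded as count data, Poisson models will be used". Mixed effects are added for repeated measures. The section states intention to treat, and it limits multiple imputation to sensitivity analyses where missing at random can be assumed. It names no time-to-event method, and it does not say whether days to healing is an interval or a count outcome.

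**The concern.** A child whose wound is grafted before it reaches 95% has no healing day, and neither has a child lost or discontinued before healing. A linear or Poisson model of days needs a number for each child, so these children either fall out of the main analysis or receive an imputed value.

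Grafting plausibly marks slow healing. Leaving grafted children out would then trim the slow tail, and trim it more in the arm that heals more slowly. That biases the healing comparison towards no difference. Imputation under missing at random does not clearly repair this, because the reason for the missing value is closely tied to the value itself.

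A second problem would arise only if days were treated as counts. Plain Poisson fixes the variance at the mean, and its standard errors are too small if healing times vary more than that.

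**Working it through.** **The plan's own figures.** The article gives no sample size or SD for healing time. Its only calculation is for pain: SD 2.4, difference 1.8, power 0.8, alpha 0.05 (two-sided assumed). A t-test calculation gives 28.9, so the stated 29 per arm is reproduced. The trial is not sized on healing, so no corrected sample size follows from this point.

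The one source on the spread of healing times is the earlier distraction trial described in Distraction, pain and wound healing: 2.1 days faster, interval −4.38 to 0.10, p = 0.061.

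- SE, if the interval is 95%: (4.38 + 0.10) / (2 × 1.96) = 1.14 days.
- Check: the midpoint is −2.14, and 2.14 / 1.143 = 1.87, which gives p = 0.061. This matches the stated value and supports reading the interval as 95%.

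**Bias from leaving out grafted children (simulation).** All inputs are assumptions except the 36 per arm and the 2.1-day difference. Healing times are log-normal with means 13.8 and 11.7 days and CV 0.35 or 0.5. Of the children unhealed at day 14, 0, 20, 40 or 60% are grafted. There were 1,500 runs per setting. Results with the true difference of 2.1 days, grafted children left out:

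| Grafted among those unhealed at day 14 | Left out of all children | Difference seen, CV 0.35 | Difference seen, CV 0.5 |
|---|---|---|---|
| 0% | 0% | 2.08 | 2.10 |
| 20% | about 6% | 2.01 | 1.97 |
| 40% | about 13% | 1.78 | 1.74 |
| 60% | about 20% | 1.53 | 1.57 |

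The loss runs from (2.1 − 2.0) / 2.1 = 5% to (2.1 − 1.55) / 2.1 = 26%. With no treatment effect, the same grafting fractions remove about 8, 16 and 24–25% of children.

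**Type I error and power in the same simulation.**

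- With no true difference, a t test on healed children rejected in 4–6% of runs. A log-rank test that kept grafted children at risk as not healed also rejected in 4–6%.
- Plain Poisson on healed children rejected in 10–13% at CV 0.35 and 22–28% at CV 0.5.
- With the largest share grafted, power was 0.33 (t test) against 0.40 (log-rank) at CV 0.35, and 0.20 against 0.23 at CV 0.5. With few or no grafts the two were close, and the log-rank was sometimes slightly lower.

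**Poisson error by formula.** Type I error = 2 × (1 − Φ(1.96 / √(SD² / mean))). It exceeds 5% once SD exceeds √mean: √12 = 3.5 and √14 = 3.7 days.

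- Mean 12: 0.024 at SD 3, 0.09 at SD 4, 0.17 at SD 5, 0.26 at SD 6.
- Mean 14: 0.067 at SD 4, 0.14 at SD 5.
- The earlier trial's SE implies SD = 1.143 × √(n / 2). The article gives no group sizes; for an assumed 20 to 50 per arm, SD is 3.6 to 5.7. The low end sits at the threshold and the rest lies above it.

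**The case against.** The strongest reply is about scope. This is a condensed article, its Data analysis paragraph covers many outcomes at once, and rules for grafting and censoring often sit in an analysis plan that is not shown. That plan may already settle the matter. But the paragraph is not silent: it fixes a mapping from outcome type to model, and an outcome in days can enter that mapping only as interval or count. Followed as written, it leaves the problem in place.

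A second reply is that the listed methods can do more. A logistic model of healing by a fixed day would keep grafted children as not healed, and mixed models of percentage healed would use a lost child's earlier visits. Both are true, but the outcome is defined as days, and the article commits to neither for it.

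Several stronger readings are tempting, and the objections to them stand:

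- *The plan excludes grafted children.* It states no exclusion and claims intention to treat. Their omission follows from what the models need.
- *The plan uses Poisson for days and so produces false positives.* Days are never called a count, and the linear clause fits at least as well. The linear model held its error near 5%; its problem is bias. Poisson inflation depends on an SD that the documents do not give.
- *The effect could be halved or reversed.* Halving needs a harsher assumption, such as every wound unhealed at day 21 being grafted and left out. No calculation showed a reversal. Burns of 20% or more of body surface, and children needing initial theatre care, are already excluded, so grafting may be uncommon.
- *A fifth of children will lack a healing day.* The phrase "With up to a potential 20% loss to follow-up" is an allowance in a sample size for pain, not a forecast of loss before healing.

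**Conclusion.** The concern holds in a limited form. The article defines a time to event, says that wound imaging ends at healing or grafting, and then names only models that cannot use a child without an observed healing day. Neither the intention-to-treat statement nor a missing-at-random sensitivity analysis closes that gap.

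Under the assumed log-normal times, attenuation is about 5% to 26% as the share left out rises from about 6% to 20% (up to 25% where there is no treatment effect). With few grafts the practical effect is small. The figures depend on the assumed grafting pattern, since no grafting rate is given. Poisson inflation is conditional on days being modelled as counts and on SD exceeding about 3.5–3.7 days; the earlier trial makes that likely, not certain.

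The point concerns a secondary outcome that carries the second hypothesis. It should be corrected, but it does not touch the primary pain analysis.

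**What to change.** In Data analysis, name a time-to-event analysis for days to 95% re-epithelialisation:

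- Compare arms on the cumulative incidence of healing, adjusted for or stratified by pain-risk stratum.
- Treat grafting as a competing event, so that grafted children stay in the analysis as not healed. Plain censoring at grafting would be informative.
- Censor children lost or discontinued before healing at their last assessment, and report their number by arm. The discontinuation rule in Adverse effects is written for the hydrogel only, so this censoring may not be balanced.
- Add an interval-censored model as a sensitivity analysis, because healing is seen only at dressing changes and standard Cox or log-rank methods do not allow for that.
- Do not use plain Poisson for days.

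The cost is wording and slightly more analysis work on dates already collected, in Stata, which the plan already names. The downside is that the effect is no longer reported simply as a mean difference in days.

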## Discussion

Pain and distress following first aid remains a major challenge when treating acute paediatric burn injuries, and literature shows that increased pain and stress can have maladaptive effects on wound healing [35, 37, 67] and patient outcomes [68]. Although Burnaid® hydrogel dressings are frequently being used by Queensland Ambulance Services during patient transport to hospital for burn injuries [18], a limited number of high-level studies have been conducted examining the clinical utility of these dressings, particularly in relation to analgesic properties and wound-healing effects. The widespread use of hydrogel burn dressings (such as Burnaid®, BurnShield®, and Water-Jel®) is alarming owing to the lack of research supporting their use as a first aid dressing [69]. This randomised controlled trial will provide high-level evidence to determine if Burnaid® hydrogel dressing provides superior pain relief in comparison to plastic wrap as an acute burn wound covering applied after first aid in paediatric patients with thermal burn injuries. Establishing which dressing is more effective in reducing acute pain is critical to clinical care and also to facilitate further evidence-based guidelines in this field.

Burns are a painful and traumatic experience, particularly in children. Considering the adverse psychological and physiological effects secondary to pain, optimal pain management should be viewed as an essential and requisite component in acute paediatric burn treatment [9]. Reduced pain and anxiety positively influences re-epithelialisation rates [3], and time to re-epithelialisation is a good predictor of scar outcome in patients with burn injuries [70]. This further validates attempts to speed up re-epithelialisation rates. Even if hydrogel products are more expensive than current standard acute wound coverings, the cost of treating adverse scarring is substantial in resources and time, as well as in cosmetic outcome for the patient. Burnaid® hydrogel dressings have been shown to be effective evaporative cooling agents, which is why these dressings are hypothesised to have an analgesic effect during acute burn care [69].

## Trial status

Recruitment will commence at the beginning of September 2017, and it is expected that recruitment will take approximately 12 months to complete, with final data collection occurring in January 2019.

## Abbreviations

BBSIP: Brisbane Burn Scar Impact Profile
CHU9D: Child Health Utility 9D Index
COD: Change of dressing
CRW: Cold running water
DEM: Department of Emergency
EMS: Emergency medical services
FLACC: Face, Legs, Activity, Cry, Consolability scale
FPS-R: Faces Pain Scale–Revised
HREC: Human Research Ethics Committee
LCCH: Lady Cilento Children’s Hospital
NRS: Numeric Rating Scale
OPD: Outpatient department
POSAS: Patient and Observer Scar Assessment Scale
SPIRIT: Standard Protocol Items: Recommendations for Interventional Trials
TBSA: Total body surface area
TPIS: Toronto Paediatric Itch Scale
VAS: Visual analogue scale
VASobs: Visual analogue scale observer
VAS-P: Visual analogue scale for pain
